#### Cost-effectiveness analysis

The cost-effectiveness analysis will be conducted to examine the direct costs, from a societal perspective, to women and their families, maternity and child health care services and other community services in relation to pregnancy and birth. We will compare the mean costs per mother/infant pair between Birthing in Our Community (Group 1) and the Ngarrama Service (Group 4) to standard care group (Group 2 and 5) up to 6 weeks postpartum. Costs will be calculated for both mother and baby to include: women and family’s out-of-pocket expenses related to clinic appointments, outpatients (ultrasound, pathology, etc.) and prescribed medicines, and hospitalisation costs. Data will be collected through routinely collected information as well as questions embedded in the 36-week antenatal and 2 month postnatal surveys. Average costs for each mother and infant for the duration of the maternity episode (i.e. from when she first confirmed her pregnancy to 6 weeks postnatal) will be calculated and compared to determine the cost effectiveness of a model of care.

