### Study design

This study underwent peer review by the funding body, the National Health and Medical Research Council*.* This study will consist of a prospective cohort study comparing:*Maternal and infant health outcomes*: women booked to receive maternity care through MMH or RBWH, by model of care and Aboriginal and Torres Strait Islander status of baby and/or mother (see Table 3). Routinely collected clinical outcomes for mothers and infants will provide data on the effectiveness of the programs since they commenced in late 2013 and be compared across groups for the duration of the study (ending in 2019), and to baseline data for both hospitals (2009–2013). Infant assessments will be undertaken at two and 6 months postnatally for Groups 1 and 4.*Service acceptability, effectiveness and cost-effectiveness:* Maternal surveys will be undertaken as early as possible antenatally (~ 20 weeks and 36 weeks antenatally, two and six months postnatally). An ethnographic component will also explore the pregnancy and early parenting (to six months postnatal) experiences of ~ 20 women from each Birthing in Our Community and the Ngarrama Service using a longitudinal, ethnographic approach: ‘Tell My Story’ substudy. Cost-effectiveness analysis will be conducted from the broader ‘societal’ perspective which will include not only the cost to the hospital (Routine data) but the cost to the women (Women’s surveys) and partner organisations (Routine data).*Service sustainability and feasibility:* Staff perspectives and experiences will be compared across the services to determine the sustainability and feasibility from a workforce perspective.

**Table 3 Tab3:** Timeline of groups by model of care and research data available

Year	2009	2010	2011	2012	2013	2014	2015	2016	2017	2018	2019
Groups by model of care						Group 1: Birthing in Our Community, MMH (Indigenous)					
	Group 2: Standard care, MMH (Indigenous)										
	Group 3: Standard care, MMH (Non-Indigenous)										
						Group 4: Ngarrama Indigenous Maternity Service, RBWH (Indigenous)					
	Group 5: Standard care, RBWH (Indigenous)										
	Group 6: Standard care, RBWH (Non-Indigenous)										
Research data (Groups)	*Baseline*					*Study period*					
	Routine Data (2, 3, 5, 6)					Routine Data (1–6)					
						Women’s Surveys (1, 2, 4, 5)					
						Tell My Story (1, 4)					
						Infant Assessments (1, 2, 4, 5)					
						Staff Interviews (1, 4)					

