### Data collection

#### Routinely collected clinical and costing data

Data for each mother/infant dyad at the MMH will be collected from several sources. MMH obstetric (MatriX), neonatal database and expenditure data (Australian activity based funding Diagnosis Related Groups [DRG] codes) will provide detailed patient-level information on inpatient contacts for the mother and baby. Routinely collected data including expenditure data will be collected from the RBWH where it will be coded before being merged with the study database. Perinatal data will also be extracted from the Queensland Health database.

The IUIH (MMeX) and ATSICHS (Medical Director and Pracsoft; MMeX) routinely collect data on service delivery (access, clinical data, e.g. immunisations, and expenditure data) which will also be collected. The clinical and costing outcomes data will be derived from routinely collected information and survey data.

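### As worded, the cost analysis sets each single-hospital programme against a standard-care group from both hospitals, so part of any hospital cost difference would be read as a model-of-care effect

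*Protocol article*

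**What the plan says.** The Cost-effectiveness analysis section fixes the contrast in one sentence. It begins "We will compare the mean costs per mother/infant pair between Birthing in Our Community (Group 1) and the Ngarrama Service (Group 4") and goes on "to standard care group (Group 2 and 5) up to 6 weeks postpartum". The same section then treats the compared averages as showing whether a model of care is cost-effective.

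Table 3 (Study design) gives the hospital of each group:

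- "Group 1: Birthing in Our Community, MMH (Indigenous")
- "Group 2: Standard care, MMH (Indigenous")
- "Group 4: Ngarrama Indigenous Maternity Service, RBWH (Indigenous")
- "Group 5: Standard care, RBWH (Indigenous")

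The section on routinely collected clinical and costing data describes a separate source for each hospital. For MMH it lists "MMH obstetric (MatriX), neonatal database and expenditure data". For RBWH it says "Routinely collected data including expenditure data will be collected from the RBWH where it will be coded before being merged" with the study database.

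The Quantitative part of Data analysis and management plans regression and propensity score matching against confounders. Its examples are characteristics of the women (age, parity, body mass index, smoking, obstetric history). It does not name hospital.

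**The concern.** Group 1 exists only at MMH and Group 4 only at RBWH. If the comparator mixes both hospitals, each programme is measured partly against women treated at the other one. Any difference in cost level between the hospitals, whatever its cause, then enters the incremental cost of each programme, with opposite signs for the two.

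The article gives some reason to expect a difference in measured cost. Expenditure comes from separate hospital systems. Table 2 also describes a co-located Birth Centre open to eligible Group 4 women at RBWH and none for Group 1 at MMH, and it says the place of birth under standard care follows the hospital.

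The economic impact of the new model is one of the stated aims, and the Discussion makes transfer to other settings depend partly on return on investment. A contrast that makes one programme look cheap and the other dear because of where they are housed would bear directly on that conclusion.

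**Working it through.** The article states no cost mean, standard deviation, difference or cost sample size, so there is no planned figure to reproduce. The check is algebra plus an illustration.

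**Inputs.** The hospital of each group is from Table 3. The comparator is from the Cost-effectiveness analysis section. Three quantities are not in the article and are left as symbols:

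- m, the mean standard-care cost at MMH
- D, the mean standard-care cost at RBWH minus m
- w, the share of the pooled standard-care group that comes from RBWH (Group 5)

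**Pooled contrast with no true effect of either model.**

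- Groups 1 and 2 have mean m. Groups 4 and 5 have mean m + D.
- Pooled comparator = (1 − w)m + w(m + D) = m + wD.
- Group 1 minus pooled = m − (m + wD) = −wD.
- Group 4 minus pooled = (m + D) − (m + wD) = (1 − w)D.
- The gap between the two results = (1 − w)D − (−wD) = D, whatever w is.

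Each contrast takes in only the share of D that matches the other hospital's part of the comparator. Under no true effect, the ranking of the two programmes against standard care is the ranking of the hospitals.

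**Illustration.** D and w are assumed. The middle value of w is 350/770 = 0.455, the ratio of the article's overall recruitment targets (350 at RBWH, 420 at MMH), used only as a convenient mid-range value. Amounts are in AU$.

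| D | w | Group 1 minus pooled | Group 4 minus pooled |
|---|---|---|---|
| 500 | 0.25 | −125 | +375 |
| 500 | 0.455 | −227 | +273 |
| 500 | 0.75 | −375 | +125 |
| 1,000 | 0.25 | −250 | +750 |
| 1,000 | 0.455 | −455 | +545 |
| 1,000 | 0.75 | −750 | +250 |
| 2,000 | 0.25 | −500 | +1,500 |
| 2,000 | 0.455 | −909 | +1,091 |
| 2,000 | 0.75 | −1,500 | +500 |

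If RBWH is the cheaper hospital, D is negative and all signs reverse.

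**Same-hospital contrast.** Group 1 minus Group 2 = m − m = 0, and Group 4 minus Group 5 = (m + D) − (m + D) = 0, for any D and w. A cost regression with an intercept, a hospital term and one term per programme has four parameters for four group means. Before covariates are added, it therefore returns exactly these two differences.

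**The case against.** **The pooling is inferred.** No sentence says that Groups 2 and 5 will be merged. The order runs in parallel (1 and 4, then 2 and 5), so the authors may have meant Group 1 against Group 2 and Group 4 against Group 5. That reading is possible but not written. The comparator is a group in the singular, with nothing to mark a pairwise reading, so pooling is the natural sense. If pairs were meant, the sentence still needs correcting.

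**The general adjustment may cover cost.** Cost per mother and infant is a listed secondary outcome, linear regression suits it, and the confounder list is given by example. Hospital could be fitted, since standard care exists at both sites. But the analysis paragraph is framed around clinical outcomes and the examples are women's characteristics. The cost section describes only averages being calculated and compared. The coverage may be intended, but it is not stated.

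**Covariate detail belongs in an analysis plan.** This is fair as far as a bare omission goes. The point here is the comparator that the article does fix.

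**Stronger readings that the article does not support:**

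- A reader might infer that the whole hospital difference enters each contrast. Only the other hospital's share does.
- A reader might take 350/770 as the actual mix. Those are overall targets tied to the programmes, and 420 is 350 × 1.2. No Group 2 or Group 5 count is given.
- A reader might take the RBWH wording about coding as evidence of different cost coding. It may only mean replacing identifiers, which is how the article uses the word elsewhere.
- A reader might regard the same-hospital comparator as free of bias. Women in Groups 2 and 5 did not use the Indigenous-specific service at their own hospital, so self-selection remains.

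**Conclusion.** The point holds in a limited form. As worded, the cost contrast sets single-hospital programmes against a two-hospital comparator and names no hospital term. With no true model effect, Group 1 would show −wD and Group 4 would show +(1−w)D.

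The size cannot be determined, because the article gives neither D nor w, nor even the sign of D. If the hospitals cost the same, there is no bias. The table shows how the bias scales and does not estimate it.

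The conclusion rests on two assumptions: that the comparator is pooled, as the sentence reads, and that hospital is not among the adjustment variables, as none is named. It does not show that the economic result will be wrong. It shows that the stated contrast cannot separate the model from the hospital, although the design already contains the groups that would.

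**What to change.** Reword the Cost-effectiveness analysis section so that the contrasts are Group 1 versus Group 2 at MMH and Group 4 versus Group 5 at RBWH. Alternatively, specify a regression of cost on model of care with hospital as a fixed effect. State that the confounder adjustment in the Quantitative section applies to cost as well, because selection into the programmes within each hospital is not removed by matching on site. If one overall figure is wanted, combine the two within-hospital differences rather than pooling the comparators.

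The change needs wording only and no new data. Each contrast uses a smaller comparator, so the cost intervals are somewhat wider. If all groups had the same size n and the same spread σ (an assumption, since no such figures are given), the variance of a difference would rise from σ²(1/n + 1/(2n)) = 1.5σ²/n to 2σ²/n. The standard error would then grow by a factor of √(2/1.5) = 1.15. The increase is larger if the same-hospital standard-care group is small.

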Culturally safe aspects of care (importance, satisfaction)	✓		✓	
Felt respected & understood by hospital staff (by area)			✓	
Felt treated poorly or judged by staff			✓	
Satisfaction with care, recommend to others		✓		
Known midwife present during labour/birth			✓	
Attendance of group antenatal classes		✓		
Smoking				
Current smoking status, including number of cigarettes per day	D	✓	✓	✓
Attempts to quit	D	✓		
Advised to quit by health staff		✓		
Smoking support received, perceptions		✓		
Smoking household members	✓	✓		✓
Feeding baby				
Previous breastfeeding experiences, inc. difficulties	D	✓		
Intentions to breastfeed, inc. duration	D	✓		
Confidence to breastfeed		✓		
Experience of breastfeeding, inc. initiation			✓	
Use of formula, inc. reasons, age of baby			✓	
What baby has been fed in past 24h			✓	✓
Where received feeding information			✓	
Use of commercial baby food				✓
Reasons for starting solids				✓
Partner involvement				
Partner’s feelings about pregnancy	✓			
Baby’s father & father figures (involvement, attended visits, support services)				✓
Social and emotional wellbeing				
Negative life events - full extended version	✓	✓		✓
Additional worries experienced	✓	✓		✓
Family separations			✓	
Positive wellbeing scale	✓	✓	✓	✓
Modified Kessler Psychological Distress Scale (K5)	✓	✓	✓	✓
Edinburgh Postnatal Depression Scale	D			✓
Practical Social Support Scale	✓			
Social support available, inc. partner		✓		
Out-of-pocket costs				
Time spent, support person, carer, transport, food & drink		✓		
All services accessed for pregnancy/birth/baby, number of visits, out of pocket cost per visit (i.e. not refunded by Medicare)			✓	
Out of pocket cost of medicines during pregnancy/birth/baby			✓	
Infant development				
Ages and Stages Questionnaire			✓	✓
Bayley III Cognitive, Language and Motor Skills (face-to-face assessment)				✓

Note: D = clinical data available

Participants will be provided with an AU$10 gift card after completing the booking-in and 36 weeks antenatal surveys and a large tote bag at 36 weeks. An AU$30 gift card and a small toy or bib/blanket will be given for the two and six-month postnatal surveys to thank women for their time. Women who participate with their infant in the Bayley assessment will receive an additional AU$10 gift card upon completion.

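### Cost-effectiveness is to be judged from mean costs alone, and the infant cost horizon is 28 days in one section and 6 weeks in another

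*Protocol article*

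**What the plan says.** The Cost-effectiveness analysis section opens: "The cost-effectiveness analysis will be conducted to examine the direct costs, from a societal perspective". The contrast it sets is in mean cost: each of the two Indigenous-specific services (Groups 1 and 4) against standard care at the two hospitals (Groups 2 and 5), with costs followed until 6 weeks after birth. The decision rule comes last. Costs are averaged over an episode that runs "from when she first confirmed her pregnancy to 6 weeks postnatal". The section then states that these averages, for mother and infant alike, "will be calculated and compared to determine the cost effectiveness of a model of care". It names no clinical effect, incremental ratio or net benefit. The Study design section, where it describes this analysis, lists only whose costs are counted.

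The Secondary outcome measures section also defines cost for the mother and infant pair, but with split limits: the mother to six weeks and the baby to 28 days after birth.

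On sources, the article says that at the Mater Mothers' Hospital "expenditure data (Australian activity based funding Diagnosis Related Groups [DRG] codes) will provide detailed patient-level information on inpatient contacts". It does not say whether an admission still running at the horizon is cut, prorated or counted whole.

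Cost-effectiveness is a named aim in the Abstract and under Aims. The Abstract's Methods paragraph, however, describes the economic work as a comparison of costs.

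**The concern.** Two statements in the article are at fault; neither is a matter of detail left to a fuller plan.

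First, the rule for judging cost-effectiveness uses costs only. A difference in mean cost answers the question if the models are equally effective, or if the cheaper one is at least as effective. The study is designed on the expectation that effects differ. If a new model costs more and prevents preterm births, the rule cannot say whether the extra spending is worthwhile. The Discussion ties transfer of the model to other settings to its return on investment, so the conclusion carries weight.

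Second, the same cost outcome has two end points for the infant. With nothing to reconcile them, the choice could be made after the costs have been seen. The choice bears on babies who use care between the two dates, including those still in the nursery.

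**Working it through.** **Inputs**
- Decision rule and comparison groups: Cost-effectiveness analysis section.
- Infant horizon A: 6 weeks, same section.
- Infant horizon B: 28 days, Secondary outcome measures.
- Planned effect on preterm birth: 16.0% to 9.0%, 350 per cohort, power 0.801, Table 4.
- Lengths of nursery stay, and the treatment of admissions that cross the horizon: not given.

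**Step 1: does the plan really rest on unequal effects?** Reproducing the preterm row of Table 4 with a two-sided 5% normal-approximation test:
- Pooled proportion: (0.16 + 0.09)/2 = 0.125.
- Null standard error: √(2 × 0.125 × 0.875/350) = 0.0250.
- Alternative standard error: √((0.16 × 0.84 + 0.09 × 0.91)/350) = 0.0249.
- z = (0.07 − 1.96 × 0.0250)/0.0249 ≈ 0.84, so power ≈ 0.801, as stated.

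The study is therefore sized on a 7-point difference in preterm birth. Equal effects are not its working assumption.

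**Step 2: what the cost-only rule can and cannot decide.** Let ΔC be the incremental mean cost per pair and ΔE the reduction in the preterm proportion.
- ΔE = 0: the sign of ΔC is enough.
- ΔE > 0 and ΔC < 0: the new model dominates, and cost alone happens to give the right answer.
- ΔE > 0 and ΔC > 0: the answer depends on ΔC/ΔE. At the planned effect, ΔE = 0.16 − 0.09 = 0.07, so the cost per preterm birth averted is ΔC/0.07 ≈ 14.3 × ΔC.

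The stated rule looks only at ΔC. In the third case it ranks the new model as worse without any value being placed on the births averted.

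**Step 3: the two horizons.**
- Analysis section: 6 × 7 = 42 days, for mother and infant.
- Outcome list: 28 days for the infant, six weeks for the mother.
- Difference: 42 − 28 = 14 days for the infant, so the shorter horizon is 14/42 = one third shorter. The mother's horizon agrees.

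**Step 4: long stays.** If inpatient cost is assigned by day and cut at horizon H, a stay of S days loses max(0, S − H) days. This is positive for S > 28 under one definition and for S > 42 under the other, so neither limit is free of it. If the whole birth admission is booked as one DRG-coded episode, the loss for that admission is zero. With neither S nor the booking rule given, the effect on a group mean cannot be calculated.

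**The case against.** The strongest reply is that this is a condensed article. The Quantitative section links clinical and other data to enable the economic analyses, compares effects across the groups and plans regression adjustment. A reader would see the preterm result beside the cost result, and the ratio and its uncertainty could sit in a fuller plan. That stands as far as it goes: the materials for a proper analysis are there, and the fix is small. It does not rescue the sentence that makes the cost comparison itself decide cost-effectiveness, and it does not touch the conflict in horizons.

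A reader might go further in three ways that the documents do not support.

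- **That truncation biases the result against a successful programme by a sizeable amount.** No lengths of stay are given, DRG-coded costing may not prorate at all, and Table 4 gives only births before 37 weeks, with nothing on very preterm births by group. Multiple births and infants with identified anomalies are excluded unless otherwise noted, as are transfers in for higher-level care, which may remove some long stays. Neither the size nor the direction in the group means is established.
- **That costs are lost for women who give birth before the 36-week survey.** Table 5 does place "Time spent, support person, carer, transport, food & drink" in that survey only. But out-of-pocket costs for services and medicines are asked at two months, so only the time, travel and carer items are exposed. Those items would be missing rather than zero, and a shorter pregnancy leaves less time to accrue them, so the direction of any bias is not shown.
- **That the study cannot address cost-effectiveness at all.** It can, with the data it already plans to link. What fails is the rule as written.

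**Conclusion.** The point holds in two parts, both on the text. The stated rule cannot establish cost-effectiveness when effects are expected to differ, here by 7 percentage points in preterm birth on the plan's own assumption. The infant cost horizon is stated as 28 days and as 42 days.

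The possible omission of birth-admission cost at either cut-off is conditional on admissions being prorated at the horizon. Its size is unknown and should not be given as a percentage.

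The clinical primary outcomes are unaffected. A named aim is affected, and the correction is cheap, so it should be made.

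**What to change.** 1. **Horizon.** State one infant horizon in both the secondary outcome list and the Cost-effectiveness analysis section. The preferred form is 6 weeks or the end of the birth admission, whichever is later, with the mother's 6 weeks unchanged. Say whether admissions that cross the horizon are counted whole or prorated. Infant length of stay is already a listed outcome.
2. **Decision rule.** Replace the last sentence of the Cost-effectiveness analysis section. Report the adjusted incremental cost jointly with the adjusted incremental effect on one named primary outcome, for example cost per preterm birth averted. Use the same comparison groups for both, and obtain uncertainty by bootstrapping cost and effect together.
3. **Alternative to 2.** If no effect is to be joined to cost, call the analysis a cost comparison throughout and drop the cost-effectiveness conclusion.

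The cost is some wording, a little more analysis on data already planned for linkage, and a commitment to one effect measure out of four primary outcomes. That last choice is a real one and should be fixed before costs are compared.

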#### Qualitative

Qualitative interview data from the Tell My Story study will be audiotaped, as will staff focus groups and interviews. Data will be analysed using Interpretative Phenomenological Analysis (IPA), a qualitative method of analysis which draws knowledge from everyday experiences and is descriptive. Transcripts will be read by a minimum of two team members who will identify key themes and independently create a coding system. Codes will be compared, inconsistencies discussed and reconciled, and a final coding scheme agreed before entry into NVivo Version 8. The analysis will comprise of: Firstly, coding of initial interview transcripts to identify themes and develop a coding framework. Secondly, identification and categorisation of women and staff experiences using the coding framework. The coding framework will be revised and refined as new themes emerge. Finally, key findings will be used to inform the development future Birthing on Country services. Data will be saved on the computer hard drive and transcribed verbatim.

